**For Control Group**

Control cohort receives the same intervention material along with practical on the performance of BSE right after the collection of the second post-intervention follow-up response from both groups.

topics as the baseline assessment to track changes in knowledge, beliefs, and practices

## 2.13 Retention of Participants

To overcome the attrition, various participants will be followed to retain the participants till the end, detailed information regarding the participant's contact will be acquired, like enrolment number, contact number, and email address will be obtained from the participants, and the researcher will make sure nobody else can have access to them. The researcher will share her contact number and email address for any correspondence associated with the BSE examination.

## 2.14 Evaluation of the Educational Intervention

For both groups, evaluation follow-up will be accomplished in one month, and a month follow up. Content of the follow-up questionnaire assessment will be the same as of the baseline questionnaire, except for section one, which will be omitted from the follow-up assessment. The differences among both groups for breast self-examination practice, knowledge and beliefs associated with breast cancer, will be assessed by statistical tests.

## 2.15 Development and validation of intervention module

Integrating guidelines from the American Cancer Society (ACS) into our intervention module for breast cancer screening will represent a pivotal step in ensuring credibility and effectiveness. The ACS, renowned for its expertise in cancer research and prevention, provides evidence-based recommendations crafted by leading breast cancer experts. This integration will not only bolster the module's validity but also align our efforts with globally recognized standards for breast cancer screening and prevention (Rock et al., 2020).

The ACS guidelines will serve as a benchmark for promoting consistency and best practices in our intervention. Regular updates based on the latest scientific research will ensure that our module incorporates current knowledge and advancements in the field, thereby enhancing its relevance and reliability (R. A. Smith & K. C. Oeffinger, 2020). By adhering to these guidelines, our intervention will not only educate but also empower participants with accurate, up-to-date information critical for making informed decisions about breast cancer screening (Desreux, 2018).

Furthermore, grounding our intervention in the Health Belief Model (HBM) will provide a robust theoretical framework for understanding and influencing health behaviors related to breast cancer screening. The HBM emphasizes individual perceptions of susceptibility to breast cancer, the seriousness of the disease, and the perceived benefits and barriers to screening (Rezano et al., 2022). By addressing these factors, our intervention aims to modify beliefs and attitudes, thereby fostering a proactive approach to breast cancer prevention among teachers in our study.

By addressing these factors, our intervention aims to modify beliefs and attitudes, thereby fostering a proactive approach to breast cancer prevention among teachers in our study. The intervention protocol will include a comprehensive educational module delivered through multimedia presentations, skill-based training sessions, informative leaflets, and engaging videos on breast health and self-examination. Additionally, practical aids such as breast cancer logo wall hangings and reminder messages via WhatsApp will aim to reinforce the importance of regular self-examination (Ştefănuţ & Vintilă, 2022). Participants will also receive small souvenirs featuring breast cancer awareness messages, serving as daily reminders to prioritize their health.

The development of the educational module will undergo rigorous validation processes, including content validity checks by experts from the Community Health Department. Their feedback will ensure that the module effectively conveys essential information and addresses potential cultural sensitivities and barriers to screening (Pucha, 2022).

In summary, by integrating ACS guidelines and leveraging the HBM, our intervention module aims to educate and empower participants to take proactive steps towards breast cancer screening. Through a robust educational approach and rigorous validation processes, we strive to enhance awareness, promote early detection, and ultimately reduce the burden of late-stage breast cancer diagnoses in our community

## 2.16 Operational Definitions of Variables

**13.15.1 Dependent Variables**

**1. Practice of Breast Self-Examination (BSE)**

- **Frequency of BSE:** Participants will be categorized as practicing BSE regularly (once a month or more) or irregularly (occasionally or less).
- **Performance of BSE:** Participants will be assessed on their knowledge of how to conduct BSE through a series of questions.

**13.15.2 Independent Variables**

**a. Educational Intervention on Breast Cancer and BSE** The intervention group will receive a PowerPoint presentation, hands-on training using a breast model, and additional materials (leaflet, short film, wall hanging, SMS reminders). The control group will receive no intervention.

**b. Sociodemographic Characteristics**

- **Age:** Calculated as the difference between birth year and the study year. Participants must be 25 years old or older.
- **Years of Teaching Experience:** Self-reported by participants.
- **Monthly Income:** Categorized into low, middle, and high income based on World Bank income levels
- **Education Level:** Highest educational qualification achieved (PhD, Master's, Bachelor's).
- **Marital Status:** Self-reported as single, married, divorced/separated, or widowed.
- **Religion:** Self-reported as Islam, Christianity, Hinduism, or other.
- **Native Language:** Self-reported from a list of options.
- **Presence of Female Doctor/Health Personnel in Immediate Family:** Yes or no.
- **Area of Residence:** Categorized as rural or urban.
- **Family History of Breast Cancer:** Self-reported as yes or no.
- **Personal History of Benign Breast Diseases:** Self-reported as yes or no.

## Data Summarizing and Analysis

The statistical analysis for this study will be conducted using IBM SPSS Statistics software, version 26.0. Before performing any statistical tests, continuous variables will be evaluated for their distribution characteristics. Variables that display a normal distribution will be summarized using descriptive statistics such as mean and standard deviation. In contrast, continuous variables that do not follow a normal distribution will be described using the median and interquartile range (IQR).

For categorical or dichotomous data, descriptive statistics will include percentages, counts, or proportions to effectively summarize the data. Statistical comparisons between categorical data from the intervention and control groups will be conducted using Chi-square tests or Fisher's exact tests, as appropriate. Differences in means of normally distributed continuous variables between these groups will be assessed using independent-samples t-tests. Meanwhile, non-normally distributed continuous data will be compared using the Mann-Whitney U test.

Given the clustered nature of the study design, Generalized Estimating Equations (GEE) will be employed for statistical analysis. GEE is robust for analyzing data that exhibit correlation within clusters (e.g., colleges and teachers within colleges). It will enable the assessment of group effects (intervention vs. control), time effects (pre- vs. post-intervention), and their interaction effect (group*time) over the study period.

We will analyze all the data collected from both the intervention and control groups, even if participants drop out. This approach is called Intention-to-Treat (ITT). If someone stops participating before the study ends, we will use their last recorded information to fill in any missing data. This method helps ensure that our results are accurate and unbiased, even when people leave the study early.

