# Methodology

## 2.1 Study Location

The study will be conducted in Hyderabad district, located in the Sindh province of Southeast Pakistan. Hyderabad, positioned 175 kilometers north of Karachi, ranks as the second-largest city in Sindh and the eighth largest in Pakistan, with a population of 1,732,693 as per the 2017 census (Statistics, 2017). It serves as a significant hub connecting Greater Sindh with rural areas.

Ten colleges from Hyderabad District, with 686 teachers, are included. These colleges offer intermediate and degree programs. Their programs are in three main areas: Arts, Science, and Business (Commerce). The teachers at these colleges are very well educated. Most of them have master’s degrees in their subjects, and some even have PhDs. The minimum criteria for appointment are a master’s degree in the respective field. We will conduct several preliminary steps before starting the main study, a Cluster Randomized control trial. These include a pilot study and a pretest to make sure our research tools are accurate and effective. Additionally, a cross-sectional study will be carried out to gather initial data from the same group of people who will participate in the main study.

To ensure fairness, the ten colleges will be randomly divided into different groups. Each group will participate in a specific phase of the study. This random assignment helps to prevent bias and makes the results more reliable. Among these ten, six colleges are randomly selected for the Pilot & pretesting phase and the cross-sectional phase, leaving four colleges to include in the main study.

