**Study Design:**

A single blinded, cluster randomized controlled trial (cRCT) will be carried out among female college teachers from government colleges in Hyderabad district. Colleges will serve as randomization units (clusters). The study will proceed through three phases:

**Baseline Data Collection:** Data will be collected from both control and intervention groups.

**Intervention Delivery**: The intervention will be administered to the intervention group during this phase.

**Follow-up Data Collection**: Follow-up data will be collected at two different post-intervention points: one month and three months later. The same questionnaire will be used for both control and intervention groups. The intervention module will be applied to the control group after the study's completion.

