## 2.7 Sampling Methods

A cluster sampling method will be applied, four colleges will be included in CRCT.A thorough eligibility assessment will be conducted. This evaluation will consider factors including the availability of an adequate number of qualified teachers, infrastructure needs, and study participation readiness. In the proposed research study, the following process will be followed to select a representative sample and conduct randomization for the cluster randomized trial.

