**Step 2:**

**Randomize Within Blocks:**

- Each block will be randomly assigned to one of the treatment groups. For example, flip a coin or use a random number generator to determine whether Block 1 goes to the intervention or control group, and similarly for Block 2.

**Required sample size:** The Total sample size required for the second phase of study is 114, that is 57 participants in each arm.

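### With four colleges, neither uncorrected GEE nor tests that ignore college hold 5%: false-positive rates run from near 5% to about 63%, depending on choices the plan leaves open

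*Combined protocol and SAP*

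**What the plan says.** Section 2.1 draws six of the ten colleges for earlier phases, "leaving four colleges to include in the main study". Section 2.7 confirms that "four colleges will be included in CRCT". Under Study Design, the college is the unit of randomisation. Section 2.7, Step 1 pairs the colleges into two blocks, and Step 2 adds: "Each block will be randomly assigned to one of the treatment groups". Each arm therefore holds two colleges.

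The section Data Summarizing and Analysis gives two sets of between-arm methods:

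- Tests that take no account of college. "Statistical comparisons between categorical data from the intervention and control groups will be conducted using Chi-square tests" (or Fisher's test), and "Differences in means of normally distributed continuous variables between these groups will be assessed using independent-samples t-tests", with Mann-Whitney for skewed data. Nothing limits these to baseline.
- GEE, chosen because of the clustering: "Generalized Estimating Equations (GEE) will be employed for statistical analysis. GEE is robust for analyzing data that exhibit correlation within clusters". It is to give group, time and group-by-time effects.

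The documents do not state the GEE subject (college or teacher), the working correlation, a small-sample correction, a t or F reference distribution, the coding of time, or which test is primary. Appendix II accepts that clustering exists, with an ICC of 0.02.

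**The concern.** The sandwich variance behind GEE is justified when there are many independent clusters. With two per arm it is biased downwards, and comparing the statistic with a normal or chi-square table ignores that only 2 degrees of freedom are available (4 colleges less 2 arm means). If the teacher is the GEE subject instead, correlation between colleagues is left out, as it is in the simple tests.

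What is at stake is the primary conclusion on BSE practice (section 2.8.1). A nominal 5% result could arise by chance far more often than one time in twenty. The choice of test could also be made after the data are seen.

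**Working it through.** **Inputs.** Four colleges with 31, 26, 34 and 23 sampled teachers (section 2.7, Step 3), on average 114/4 = 28.5. Two-sided 5%, 80% power, 85.6% v 26%, ICC 0.02, 20% attrition and 90% eligibility (Appendix II). Three time points (Study Summary). ICCs of 0.05 and 0.10 are assumptions, used to show a range.

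**1. The plan's own figure.** 85.6% v 26% needs 10 per arm, or 13 with continuity correction; the plan states 14. From there the chain reproduces: 28 × (1 + 98 × 0.02) = 82.88, taken as 83; 83/0.8 = 103.75, written as 103; 103/0.9 = 114.4, giving 114. The plan uses 99 teachers per college in the design effect, although about 28.5 are sampled. The sampled number is used below.

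**2. Tests that ignore college.** With D = 1 + (m − 1) × ICC, the false-positive rate is 2 × [1 − Φ(1.96/√D)].

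| ICC | m = 28.5 (all sampled) | m = 23 (about 80% followed) |
|---|---|---|
| 0 | 5.0% | 5.0% |
| 0.01 | D = 1.275: 8.3% | D = 1.22: 7.6% |
| 0.02 | D = 1.55: 11.5% | D = 1.44: 10.2% |
| 0.05 | D = 2.375: 20.3% | D = 2.10: 17.6% |
| 0.10 | D = 3.75: 31.2% | D = 3.20: 27.3% |

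Simulation with 26% in both arms and the planned college sizes agrees. At ICC 0.02 chi-square gives 10–12%, Fisher 8–9%, and, for a continuous outcome, the t-test 11.8% and Mann-Whitney 11.3%. At ICC 0.05 chi-square gives 17–22%.

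**3. GEE with college as cluster, no correction.** With K = 2 clusters per arm the sandwich variance is (K − 1)/K = 1/2 of the unbiased one, so z = √2 × t on 2 df.

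- One contrast (1 df): P(|t₂| > 1.96/√2) = P(|t₂| > 1.386) = 0.300. Fitted GEE models gave 27–38%.
- Joint group-by-time over three time points (2 df): the Wald statistic is twice Hotelling's T², and T²/4 follows F(2,1). The rate is P(F(2,1) > 5.99/8) = (1 + 2 × 0.749)^(−1/2) = 0.633. Fitted models gave 62–68%.

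The 1-df rate stayed at 29–31% in simulation for every ICC from 0 to 0.10. A nominal 95% interval for one contrast covers about 1 − 0.300 = 70%. The 2-df interval from the same data is 4.30/(1.96/√2) = 3.1 times as wide.

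**4. GEE with teacher as subject.** For a binary outcome at ICC 0.02, fitted models gave 9–11% for the group effect and 5–9% for group-by-time. The low end applies when college effects are constant over time and so cancel from the change. One run with a continuous outcome, ICC 0.05 and college effects varying over time gave 21–31%, so this branch does depend on the ICC.

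**5. College-level t-test on 2 df** (critical value 4.30). Simulated false-positive rate: 5.0–5.4% for ICC 0 to 0.10. Simulated power at 85.6% v 26%:

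| ICC | 114 teachers | 91 (20% lost) | 83 |
|---|---|---|---|
| 0.02 | 85% | 81% | 80% |
| 0.05 | 73% | 70% | 69% |
| 0.10 | 60% | 58% | 57% |

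For a 30-point difference (56% v 26%) at ICC 0.02, power is 35% with 114 teachers and 30% with 83. Suppose the 20% lost from the intervention arm carry forward a 26% rate (an assumption). That arm then falls to 0.8 × 85.6 + 0.2 × 26 = 73.7%, and power with 103 analysed is about 64% at ICC 0.02 and 51% at ICC 0.05.

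**The case against.** **The GEE subject and time coding are not fixed.** The text mentions both colleges and teachers within colleges, and describes time as before versus after, which could mean two levels. With two levels, group-by-time has 1 df and the rate is near 30%. With teacher as subject, neither 30% nor 63% applies. This stands. A reader might infer that every planned test has an error rate between 10% and 64%; the documents do not support that, and some branches lie near 5%. The silence is still a defect, because it leaves the choice open.

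**The simple tests may be meant for baseline or description.** They come before GEE, which is introduced for the clustering, so this is possible. The text does not say so, and it needs to.

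**A correction may be intended.** None is stated, so none can be credited.

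**A significant result is still some evidence.** True. A reader might infer that it would be none. At the planned 59.6-point difference even an oversized test carries some weight; what fails is its stated error rate and coverage.

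**The remedy is not free.** This also stands. A reader might infer that about 80% power is secure, but that needs ICC 0.02 and the full planned effect. New wording also does not create more colleges. The coin flip between two fixed blocks has only two allocations. Even a free 2:2 split has six, with a smallest two-sided p of 2/6 = 0.33. No randomisation test can reach 0.05, and the t-test's 5% level rests on a model.

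**Conclusion.** The point holds in conditional form and should be settled before outcome data are analysed. As written, the plan does not secure a 5% error rate for the primary comparison. The result under each reading is:

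- college as GEE cluster, uncorrected: about 30% for a 1-df contrast and about 63% for the joint 2-df group-by-time test, almost whatever the ICC;
- teacher as GEE subject, ICC 0.02: about 9–11% for group and 5–9% for group-by-time;
- tests that ignore college, ICC 0.02: about 10–12% (Fisher 8–9%), rising to about 17–22% if the ICC were 0.05.

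The first line assumes that no correction is applied. The others need an ICC above zero, which the plan itself assumes.

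**What to change.** In Data Summarizing and Analysis:

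1. Name one primary contrast: regular BSE at month 3.
2. Compute the proportion, or the mean baseline-adjusted residual, for each college. Compare arms with a two-sample t-test and 95% interval on 2 df. A model with a college effect and small-sample 2-df inference is an acceptable equivalent.
3. Analyse knowledge and beliefs the same way. Treat month 1 and group-by-time as supportive.
4. Keep the chi-square, Fisher, t and Mann-Whitney procedures out of between-arm inference: descriptive summaries only, without p-values.
5. State that the 2-df test treats colleges as exchangeable draws, since two allocations cannot support a randomisation test.
6. Report power over a range of ICCs and effects, including dilution from carrying the last observation forward.

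The change is to the text of the plan and needs no new data. The price is much wider intervals and power that may fall well below 80%. That reflects how little information four colleges hold; only more colleges would change it.

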| **Eligibility Criteria** | A. Inclusion criteria  For colleges  Willing to be a part of the study.  • For teachers  • Full-time faculty appointed in government colleges in Hyderabad district.  • Aged between 25-59 years.  • Willing to be part of the study.  B. Exclusion criteria  • For colleges  • Colleges that are not willing to participate in the study despite meeting the inclusion criteria.  • Colleges already participated in initial phases of study, pilot testing, and cross-sectional study.  • For Teachers  • Pregnant teachers and lactating mothers  • Those who are on sabbatical leave.  • Diagnosed/Recovered breast cancer patients.  • Teachers who will refuse to be part of the study |
| **Sample size** | 114 for both arms, 57 in each arm. |
| **Intervention** | Health belief theory-based breast self-examination intervention delivered to the intervention group |
| **Control Group** | Will receive the intervention at the end of the study |
| **Data Collection Points** | Baseline, post-intervention at two different time points, 1 month and 3 months. |
| **Primary Outcome** | Practice and frequency associated with breast self-examination |
| **Secondary Outcome** | Knowledge of breast cancer and breast self-examination, beliefs linked with breast cancer and breast self-examination |
| **Discussion** | This cluster randomized controlled trial aims to improve the efficacy and legitimacy of theory-based breast self-examination interventions by increasing women's knowledge of the need for breast cancer awareness and changing their attitudes to encourage early breast cancer detection. |

| Chief Investigator &Main supervisor | [name] [name] |
| --- | --- |
| Co-Investigator &Co-supervisor | [name] |
| Co-Investigator | [name] |

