**Specific Objectives**

1. To develop, validate, implement intervention, and evaluate the effectiveness of a health educational intervention in improving knowledge of breast cancer, knowledge, beliefs, and practices of breast self-examination.
2. To determine a significant association between the respondent’s characteristics, knowledge of breast cancer, knowledge, beliefs, and practices on breast self-examination among college teachers.
3. To determine the differences between and within the control, and intervention group, pre and post intervention on knowledge of breast cancer, knowledge, beliefs, and practice of breast self-examination at baseline, 1 month, and 3 months post interventions.

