### Appendix II. Sample size calculations

Phase II(CRCT)

To determine a significant association between the respondent’s characteristics, knowledge, beliefs, and practices on breast self-examination among college teachers.

Sample size calculation will be done by applying formula two proportion/two sample for t testing hypothesis and observing expected differences in proportions of BSE practice between two groups.

n = [(Z_ı - α)√(2P̅(1 - P̅)) + (Z_ı - β)√(Pı(1 - Pı) + P2(1 - P2))] / (Pı - P2)²

Table 3.3: Information of sample size derivation

| **Attribute** | **Assumptions** |
| --- | --- |
| **Z** | Cluster Randomized Controlled Trial |
| **Z(1-α)** | Zα= 1.96; p-value= 0.05; therefore, power desired is 0.95 |
| **Z(1−β)** | Zβ=0.84; β=0.20; 0.80 power was desired. (James 2001) |
| **P1** | P1=85.6% Prevalence of regular breast self-examination practice in intervention group 06 months post intervention(ABDULRAHMAN, 2020) |
| **P2** | P2=26%, Prevalence of regular breast self-examination practice in control group 06 months post intervention(ABDULRAHMAN, 2020) |

Sample size n= **14** calculated by openEpi(Charan & Biswas, 2013) 2 groups 14* 2 = 28

28 x [1 + (m-1) ICC)

Where: m=average cluster size,

ICC-class correlation coefficient m

ICC =0.02: intra-cluster correlation coefficient based on Cluster randomised controlled trial comparing the effectiveness and cost-effectiveness of two primary care interventions aimed at improving attendance for breast screening (Richards et al., 2001),

m= 99 (average cluster size calculated)

n​=28×[1+(m−1) ×ICC]

Given that average cluster size =99

ICC=0.02:

n=28× [1+(99−1) ×0.02]

n=28× [1+98×0.02]

n=28× [1+1.96]

n=28×2.96

n≈82.88

Rounding up to the nearest whole number, the final adjusted sample size without considering attrition and eligibility adjustments would be approximately 83.

To adjust for a 20% attrition rate, we need to increase the sample size by dividing it by the complement of the attrition rate, which is 1-0.2 = 0.8. So:

83 / 0.8 = 103

To adjust for the eligibility proportion of 90%, we need to further increase the sample size by dividing it by the eligibility proportion. So:

103 / 0.9 = 114

The final required sample size with attrition and eligibility adjustments is approximately 114 teachers.

114/2 =57

57 participants in each group.

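### No decisive visit or contrast is named for the primary outcome, so several unranked tests can each be read as showing effectiveness

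*Combined protocol and SAP*

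**What the plan says.** Section 2.8.1 defines the primary outcome as a binary variable, monthly BSE or not, and attaches no time point to it. The Study Summary gives the data collection points as "Baseline, post-intervention at two different time points, 1 month and 3 months"; neither follow-up visit is called primary.

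The section Data Summarizing and Analysis offers two sets of tests. The first is generic: "Statistical comparisons between categorical data from the intervention and control groups will be conducted using Chi-square tests" or Fisher's exact test. The second is a GEE, introduced because of the clustering, which is to give "assessment of group effects (intervention vs. control), time effects (pre- vs. post-intervention), and their interaction effect (group*time"). Item 3 of the Specific Objectives goes further: "To determine the differences between and within the control, and intervention group, pre and post intervention", at baseline, 1 month and 3 months. Section 2.14 says only that the differences between the groups will be assessed by statistical tests.

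None of these places ranks the tests, splits alpha or states a decision rule. The analysis section gives no significance level. The only one is in Appendix II: "Zα= 1.96; p-value= 0.05".

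**The concern.** The candidate results can disagree. Practice may differ between arms at 1 month and no longer at 3 months. The group-by-time term may be significant when the group term is not. The intervention arm may improve from baseline while the control arm improves as much. As written, the plan does not say which result then decides, so the choice can be made after the data are seen. The 5% level used to size the trial would not be the false-positive rate of that procedure.

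Some of the listed effects also do not isolate the intervention. A group effect averaged over all visits includes baseline, when no one has been treated. A time effect and a within-arm change are not comparisons between randomised arms.

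**Working it through.** **1. The level the trial was sized for.** Inputs from Appendix II: P1 = 0.856, P2 = 0.26, Zα = 1.96, Zβ = 0.84. The mean proportion is 0.558 and the difference 0.596.

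- 1.96 × √(2 × 0.558 × 0.442) = 1.377
- 0.84 × √(0.856 × 0.144 + 0.26 × 0.74) = 0.472
- n = (1.377 + 0.472)² / 0.596² = 9.62, rounded up to 10
- With continuity correction: (10/4) × [1 + √(1 + 4/(10 × 0.596))]² = 13.14, rounded up to 14, as stated
- 28 × 2.96 = 82.88, taken as 83; 83/0.8 = 103.75, taken as 103; 103/0.9 = 114.4, taken as 114

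The stated size therefore corresponds to one test at two-sided 5% with 80% power. The remark on 0.95 power in the alpha row is a slip of labelling. The calculation does not identify a decisive visit either: its input is "P1=85.6% Prevalence of regular breast self-examination practice in intervention group 06 months post intervention", and 6 months is not a visit in this trial.

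**2. False-positive rate of the listed between-arm tests.** Assumptions, none of which is in the documents: each test is individually calibrated at two-sided 5%; the arm differences at baseline, 1 and 3 months are jointly normal with equal correlation r between visits; there is no intervention effect; any significant between-arm result counts. Results are from 2,000,000 simulated draws per value of r.

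| Tests that can support a claim | r = 0.3 | r = 0.5 | r = 0.7 | r = 0.9 |
|---|---|---|---|---|
| Arm comparison at 1 and 3 months | 9.5% | 9.0% | 8.4% | 7.0% |
| GEE group effect + one group-by-time test | 9.8% | 9.8% | 9.7% | 9.8% |
| Both visits + GEE group + joint group-by-time (three-level time) | 14.1% | 13.6% | 12.9% | 11.7% |
| Both visits + GEE group + pre/post group-by-time (two-level time) | 15.2% | 14.4% | 13.4% | 11.9% |

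For the GEE rows the group effect is the equally weighted average over the three visits. That average is uncorrelated with the change contrasts, so the second row is 1 − 0.95² = 9.75% whatever r is. Only one version of the group-by-time term is counted at a time, because the plan lists one.

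**3. What the group effect estimates.** Let the intervention effect be a constant D after baseline and 0 at baseline.

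- Averaged over three equally weighted visits: (0 + D + D)/3 = 2D/3
- Averaged over a two-level pre/post factor: (0 + D)/2 = D/2
- With reference coding and an interaction in the model, the group coefficient is the arm difference at the reference time, so with baseline as reference it contains no intervention effect.

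In both averaged forms a chance baseline difference enters the estimate as if it were effect.

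**The case against.** The strongest reply is that the GEE is the real analysis. It is introduced because of the clustering, whereas the chi-square and Fisher sentence is generic, names neither BSE practice nor a visit, and could be meant for baseline comparability. That reading is possible. On a natural reading the sentence does cover a binary outcome, but even without it the GEE offers a group and a group-by-time test and does not say which decides. The rate is then about 9.7-9.8%.

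A second reply is that the visits are highly correlated, more so because missing values are filled with the last recorded one and 20% attrition is assumed. This stands as a reason to look at the lower end for the two-visit case, about 7%. It does not bring the rate to 5%.

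Third, the analysis section states no level, so 5% per test is inferred from Appendix II. That also stands, and the figures are conditional on it. Finally, the planned effect is large (85.6% against 26%); an effect of that size would probably be significant on most contrasts. The rule matters most if the effect is smaller, fades or is absent.

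A reader might go further and infer a rate of 17-18%. That figure needs interaction tests at each visit and a pooled pre/post interaction in the same family. These are alternative codings of the single group-by-time term in the plan, so they should not be added together. A reader might also infer that a rise within the intervention arm will be claimed as effectiveness. Objective 3 lists such changes, but Section 2.14 describes the evaluation as a comparison of the groups, and nothing says a within-arm change will carry the claim. How often one would be significant without any intervention effect depends on the rise in both arms, for which the documents give no figure.

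**Conclusion.** The point holds: no visit and no contrast is named as decisive for BSE practice, and nothing controls the error across the listed tests. If each test is calibrated at two-sided 5% and any significant between-arm result counts, the chance of a false claim is about 7-10% for the two visits alone (correlation 0.9 to 0.3), about 9.7-9.8% for GEE group plus group-by-time, and about 12-15% for both visits plus the two GEE tests. The ranges depend on the assumed correlation and on which tests are counted.

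They should not be read as this trial's actual error rate. Calibration at 5% is doubtful with four colleges, two per arm. For instance, a chi-square test that ignores clustering, with 114/4 = 28.5 teachers per college and ICC 0.02, has design effect 1 + 27.5 × 0.02 = 1.55 and a single-test error of about 11.5%. That is a separate problem; solving it would not say which test decides.

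**What to change.** Before outcome data are seen, add to the analysis section:

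- The trial is decided by one cluster-adjusted between-arm contrast in regular BSE practice, at one named visit, at two-sided 5%. Three months, the last visit, is one option; the documents favour neither visit.
- The other visit is tested only if the first test is significant (fixed sequence), or is labelled supportive.
- The chi-square and Fisher comparisons, the GEE group main effect, the time effect and the within-arm changes are reported as estimates with intervals and will not support a claim of effectiveness.

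The cost is a few sentences, with no added participants or data. The downside is that an effect seen only at the other visit could not be claimed as the primary result.

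If both visits must be able to carry the claim, testing each at 2.5% gives 4.9%, 4.6% and 4.3% at correlations 0.3, 0.5 and 0.7. By the plan's own method this needs 16 instead of 14 per group before inflation: 32 × 2.96/0.8/0.9 = 131.6, about 132 teachers instead of 114.

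Either route controls multiplicity only. The small-cluster calibration of the deciding test has to be dealt with separately.
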